### Interventions

The individuals in the experimental group will receive nutritional guidance from a registered dietitian at 1, 4, and 7 months after enrollment. A study has reported that nutritional guidance for 6 months or longer, or in numerous sessions, is effective for preventing weight gain and for discouraging former smokers from resuming smoking [15]. An investigator or associate will explain the significance of the nutritional guidance in this trial (preventing weight gain after SC) to a registered dietitian at each study site. Typically, food intake and the number of meals increase in response to oral cravings and increased appetite after quitting smoking. During nutritional guidance, participants will be educated on the significance of actively managing nutrition while quitting smoking. Participants’ height and weight will be determined, and they will be informed of their optimal weight based on a reasonable Body Mass Index (BMI) (22). An instructional plan to meet an individual’s estimated energy requirements and nutrient intake will be formulated based on the Dietary Reference Intake for Japanese (2015) as stipulated by the Ministry of Health, Labor, and Welfare [16]. In principle, the estimated energy requirement and nutrient intake are based on Article 20, Point 2 of the Health Promotion Act (Act No. 103 of 2002) [16]. The Dietary Reference Intakes help calculate the estimated energy requirement based on basal metabolism, physical activity level, sex, age, height, and weight. It also assesses the status of food intake, whereby changes in weight are used to assess whether the actual energy requirement is lower or higher than the estimated value. If a participant has an illness, such as diabetes, hypertension, dyslipidemia, atherosclerotic disease, or chronic kidney disease, an instructional plan will be devised based on management guidelines for that particular illness. For this, an individual’s energy needs will be determined and their dietary intake assessed so that the individual can be instructed on how to improve their diet.

During follow-up, the participants will log their dietary intake, activity level, and weight to the greatest extent possible. During follow-up, an excess or lack of energy will be assessed in light of weight changes. Targets will be reset while referring to individual logs as needed, and the participants will be encouraged to appropriately manage their energy and nutrient intake and weight. Individuals who resume smoking while receiving nutritional guidance will not be prompted to quit smoking. Items covered and materials used in nutritional guidance will be standardized among the study sites.

### Control conditions

Individuals not receiving nutritional guidance will have a follow-up visit 9 months after enrollment.

### Both groups

Studies have reported that oral antidiabetic, antihypertensive, antidyslipidemic, antipsychotic, and antiepileptic drugs, and other medications can affect weight and adiponectin levels (the primary endpoint of this trial). Thus, the baseline dosage and concomitant medications will, in principle, not be modified, nor will new medications be added during the follow-up of either group. If the baseline dosage or concomitant medications must be modified, or a new medication must be added, the reason for the change, the name of the medication, the dosage, and the duration of administration will be described in detail on the questionnaire. If a participant fails to make a scheduled visit, the individual will be contacted by telephone to ascertain the reason. Upon the conclusion of the trial treatment period, routine treatment covered by National Health Insurance will be provided as needed at the physician’s discretion.

### Items noted and studied

The following items will be assessed during the fifth visit to the SC clinic (upon enrollment) and at 9 months after enrollment:

#### Items that will only be assessed upon enrollment

Height; the number of cigarettes smoked as of the first visit to the SC clinic; the number of years of smoking; nicotine dependence (FTND score); weight gained (kg) between the first and the fifth visit to the SC clinic; the fear of gaining weight according to a survey; and the stage of behavioral change in terms of diet. A survey will be administered on paper at the start of enrollment to assess (1) the fear of gaining weight and (2) the stage of behavioral change with respect to an improved diet in order to prevent weight gain. Responses to both questions will be on a 4-point scale.

#### Items measured upon enrollment and 9 months after enrollment

Items that will be measured as part of treatment covered by National Health Insurance are medication information: (1) oral hypoglycemic drugs, (2) antihypertensive drugs, (3) antidyslipidemic drugs, (4) antipsychotic/antiepileptic drugs, and (5) the name of, and daily dose of, other medications, body composition (weight, BMI, and abdominal circumference); blood pressure and pulse rate; the concentration of exhaled carbon monoxide (CO); a self-rating depression scale; routine biochemistry: lipid profile (total cholesterol, triglycerides, high-density lipoprotein cholesterol (HDL-C), low-density lipoprotein cholesterol (LDL-C)); blood glucose; glycosylated hemoglobin (hemoglobin A1c; HbA1c); kidney function (creatinine, blood urea nitrogen, uric acid, sodium, potassium, and chloride); liver function (total protein, albumin, glutamic oxaloacetic transaminase, glutamic pyruvic transaminase, and gamma-glutamyl transferase); and blood counts: white blood cell count and appearance, red blood cell count, hematocrit, hemoglobin, and platelet count.

Items that will be measured as part of treatment but that are not covered by National Health Insurance are: high-sensitivity C-reactive protein (hsCRP) levels, oxidized LDL complexes (AT-LDL and serum amyloid A-LDL (SAA-LDL)), the LOX Index, adiponectin, and leptin.

After a participant has remained in a seated position for 5 min or longer, their blood pressure will be measured with a sphygmomanometer while keeping the heart and the measurement site (brachial artery) at the same height. Then, 20 mL of venous blood will be collected from the forearm; 10 mL of that blood will be used to perform routine biochemistry and to determine the blood counts. The remaining 10 mL will be centrifuged. A portion of this remaining blood will be refrigerated and used to measure levels of AT-LDL and SAA-LDL, and the rest will be stored in a deep freezer at − 80 °C. The cryopreserved portion will be used to measure levels of hsCRP, the LOX Index, adiponectin, and leptin.

### Observation and testing schedule

#### Primary endpoint

The primary endpoint for this trial will be the adiponectin level. Adiponectin is a peptide hormone secreted by adipocytes that inhibits atherosclerosis [17, 18]. Adiponectin is also a cardiovascular disease risk marker closely related to smoking, obesity, and atherosclerotic disease (i.e., adiponectin levels decrease as a result of smoking or obesity) [17, 18].

#### Secondary endpoints

Secondary endpoints will be the following: (1) levels of oxidized LDL complexes (AT-LDL and SAA-LDL), levels of hsCRP, and the LOX Index; (2) markers of glucose and lipid metabolism: HbA1c, LDL-C, HDL-C, nonHDL-C, and leptin levels; (3) BMI and abdominal circumference; and (4) the percentage of individuals who quit smoking for a prolonged period.

The cardiovascular risk biomarkers serving as secondary endpoints are closely associated with smoking, obesity, and atherosclerotic disease. Oxidatively modified LDL complexes (AT-LDL and SAA-LDL) promote atherosclerosis [9, 10]; AT-LDL is related to smoking status and obesity. A study has suggested that weight gain after quitting smoking might inhibit a decrease (improvement) in AT-LDL after quitting smoking [9, 10, 19]. SAA-LDL is also related to obesity and smoking [20]. Another study has suggested that SAA-LDL might be superior to hsCRP as a cardiovascular marker [21]. High-sensitivity CRP increases as a result of diabetes, obesity, smoking, or age, and hsCRP is related to atherosclerotic disease. The LOX Index is determined by multiplying the level of soluble lectin-type oxidized LDL receptor 1 (LOX-1) (an oxidized LDL receptor found in vascular endothelial cells) by the level of ligand containing ApoB (a modified LDL that binds to LOX-1). A high LOX Index is significantly related to a risk of developing cardiovascular disease, and a low LOX Index is related to a reduced risk of cerebral infarction [22]. Changes in other laboratory results from normal values could serve as the latest indicators with which to assess the progression of atherosclerosis in the future and to assess the risk of cerebral infarction or myocardial infarction in earlier stages [22]. Leptin is a peptide secreted by adipocytes that is involved in inhibiting obesity, given it has action to suppress the appetite and increase energy expenditure.

### Statistical analysis

#### Analysis set

The assigned groups, i.e., the individuals receiving nutritional guidance vs. the individuals not receiving nutritional guidance, will be compared based on the intention-to-treat principle. All data, such as levels of cardiovascular biomarkers and weight obtained from each group upon enrollment and at 9 months after enrollment, will be analyzed. Only individuals who quit smoking for a prolonged period will be similarly analyzed, and individuals who have resumed smoking will be excluded. Quitting smoking for a prolonged period is defined as, at 9 months after enrollment, indicating in an interview that one has not smoked in the past month and having a concentration of exhaled CO of 7 ppm or lower.

#### Items analyzed and analytical methods

The participant characteristics in both groups will be described statistically. Mean values for weight, abdominal circumference, changes in marker levels for glucose and lipid metabolism, along with changes in cardiovascular biomarkers from enrollment until 9 months after enrollment, will be compared between the two groups. The distribution of individual indices at baseline and at 9 months after enrollment will be determined for the two groups, and a *t* test or a Wilcoxon rank-sum test will be performed. In addition, Fisher’s exact test will compare the percentage of individuals who quit smoking for a prolonged period in the two groups. The level of significance will be 0.05 or less. A two-tailed alpha of 5% and a two-sided 95% confidence interval will be used. The statistical analysis will be performed by a statistician. The primary endpoint will be assessed statistically to facilitate an interim analysis. Nutritional guidance will be deemed effective or ineffective in the final analysis using the statistic *Z*_prop_ = 1.567. An interim analysis will be performed after the 125 participants (an intermediate number of individuals out of the total enrollment) complete follow-up. This interim analysis will determine whether to terminate this trial for efficacy or futility. Trial termination for efficacy will be based on *Z*_prop_ > 2.538, whereas trial termination for futility will be based on *Z*_prop_ < 0.698.

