**Methods/design:**

This is a multicenter, prospective, parallel-group, randomized controlled trial. Some 250 individuals who successfully quit smoking with the help of a SC clinic and who gain weight (an increase of ≥ 1.25% Body Mass Index (BMI) between the first and the fifth visit to the SC clinic) will be enrolled within 1 month of the final (fifth) visit to the SC clinic. These participants will be randomly assigned to an intervention group (125 individuals receiving nutritional guidance) or a control group (125 individuals not receiving nutritional guidance). A registered dietitian will provide nutritional guidance once every 3 months for a total of three sessions. The primary endpoint for this trial will be the level of adiponectin, a predictor of cardiovascular risk that reflects weight and smoking status. Secondary endpoints will be levels of cardiovascular, glucose, and lipid metabolism biomarkers, BMI, abdominal circumference, and the percentage of individuals who quit smoking for a prolonged period.

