### Objective of this trial

The aim of this trial is to determine and compare the effectiveness with which nutritional guidance prevents obesity after SC, the effects of nutritional guidance on cardiovascular, glucose, and lipid metabolism biomarkers, and the effects of nutritional guidance on individuals who quit smoking for a prolonged period. This trial will involve individuals who successfully quit smoking with the help of a SC clinic and gained weight.

Inhibiting weight gain after SC will help maintain glucose tolerance and prevent new-onset diabetes mellitus. An altered body composition with increased visceral fat reduces glucose tolerance while promoting oxidative stress and inflammation. However, a previous study reported that weight gain due to SC increases not only fat but also bone and muscle tissues [14]. Adiponectin levels are closely and inversely correlated with the amount of visceral fat, and numerous studies have reported that decreased adiponectin levels are associated with decreased glucose tolerance. Furthermore, adiponectin levels decrease even when weight gain is inhibited by resuming smoking. Among the numerous markers and items studied, blood adiponectin levels are particularly closely associated with abdominal obesity, smoking, oxidative stress, and obesity- and smoking-associated inflammation. Thus, adiponectin is an optimal marker for use in our study, and we have selected it as the primary endpoint.

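### BMI is a listed secondary endpoint, but the analysis section names weight instead and does not clearly say whether body measures are compared as levels or as change; a baseline-adjusted analysis of BMI and waist should be stated.

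*Protocol article*

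**What the plan says.** The first aim under Objective of this trial concerns "the effectiveness with which nutritional guidance prevents obesity after SC". The body measures chosen to address it are given twice. The abstract states: "Secondary endpoints will be levels of cardiovascular, glucose, and lipid metabolism biomarkers, BMI, abdominal circumference". The Secondary endpoints section lists "BMI and abdominal circumference" as its third item. Neither place lists weight.

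Items analyzed and analytical methods describes the between-group comparison in one sentence. It begins "Mean values for weight, abdominal circumference, changes in marker levels for glucose and lipid metabolism" and ends "along with changes in cardiovascular biomarkers from enrollment until 9 months after enrollment, will be compared between the two groups". The next sentence says "The distribution of individual indices at baseline and at 9 months after enrollment will be determined for the two groups" and that "a *t* test or a Wilcoxon rank-sum test will be performed". No baseline covariate is mentioned.

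Three other places bear on the point:

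- The Analysis set section says in general terms that all data from enrollment and 9 months will be analysed, with weight as one example.
- Items noted and studied has weight, BMI and abdominal circumference measured at both times, and height at enrollment only.
- The Randomization section gives the minimisation factors as age, sex, FTND score, weight gained around cessation, and fear of weight gain.

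**The concern.** Two things do not line up. First, the listed endpoint is BMI but the variable named for analysis is weight. Second, the analysis sentence uses *changes* for the metabolic markers and again for the cardiovascular biomarkers, but puts weight and abdominal circumference under mean values. Taken at its word, it compares levels of the body measures and changes of everything else.

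The choice between level and change matters here. Because height is recorded once, a person's BMI change is the weight change divided by a constant, so on the change scale weight and BMI carry nearly the same information. That does not hold for levels: raw weight carries all the between-person variation in height and body size. Weight, BMI and waist are not themselves minimisation factors, so a chance difference at enrollment would pass largely into a 9-month comparison of levels. Wording that supports several analyses also leaves room to choose between weight and BMI, or level and change, after the data are seen.

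**Working it through.** **The plan's own figure.** The article sizes the trial on percentage change in adiponectin only: difference 10%, SD 20%, two-sided 5%, power 80%, with an adjustment of unstated form, giving 82 per group. Without adjustment the standard two-sample calculation gives 63. Alpha 0.025 gives 77, or 81 after multiplying by π/3 for the rank-sum test, and alpha 0.05/3 gives 84. So 82 is in the range of such adjustments. Dropout: 82 / 0.75 = 109.3, rounded up to 110, as stated. No sample size or power is given for BMI, weight or waist, so there is no figure of that kind to reproduce.

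**Inputs for the illustration.**
- Analysed per arm: 125 × 0.75 = 93.75, taken as 93 (enrollment and dropout from Design and sample size).
- Two-sided alpha 0.05 (from the article).
- Weight SD s = 10-14 kg, baseline-to-9-month correlation ρ = 0.90-0.97, true difference 2 kg: all assumed; the article gives none of them.

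**Formulas.** Power ≈ Φ(d / (SD·√(2/n)) − 1.96), and detectable difference at 80% power = (1.96 + 0.8416)·SD·√(2/n), with
- raw 9-month values: SD = s
- change from enrollment: SD = s·√(2(1 − ρ))
- baseline-adjusted: SD = s·√(1 − ρ²)

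With n = 93, √(2/n) = 0.1467.

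**Central case, s = 12 kg, ρ = 0.95, d = 2 kg.**
- Raw: SE = 12 × 0.1467 = 1.76; 2/1.76 − 1.96 = −0.82; power about 20.5%.
- Change: SD = 12 × √0.10 = 3.79; power about 94.9%.
- Adjusted: SD = 12 × √0.0975 = 3.75; power about 95.4%.

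**Across the assumed range.**

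| Quantity | Raw means | Change | Baseline-adjusted |
|---|---|---|---|
| Power, 2 kg | 16-28% | 59-100% | 61-100% |
| Power, 2.8 kg | 28-48% | 86-100% | 88-100% |
| Detectable difference, 80% power | 4.1-5.8 kg | 1.0-2.6 kg | 1.0-2.5 kg |
| Power, waist 2 cm (assumed SD 9-11 cm, ρ 0.85-0.95) | 24-33% | 62-100% | 65-100% |

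Change is more precise than raw values whenever 2(1 − ρ) < 1, that is, when ρ exceeds 0.5. Baseline adjustment is at least as precise as either.

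**Baseline imbalance.** In the central case the enrollment difference in mean weight has a standard error of 12 × 0.1467 = 1.76 kg under simple randomisation. An imbalance of one standard error would carry about 0.95 × 1.76 = 1.67 kg into the raw 9-month difference, close to the 2 kg effect in the illustration. Minimising on sex, age and prior weight gain would reduce this; by how much cannot be worked out from the article.

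**The case against.** A reader might infer from the analysis section that BMI is not analysed at all. The article does not support that. The general statement about all data, and the reference to individual indices, can both include BMI. The section also summarises by category: adiponectin, the primary endpoint, is not named in the comparison sentence either.

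A reader might also take it as settled that raw weight and waist will be compared without reference to baseline. The closing time phrase, from enrollment to 9 months, can govern the whole list, which would make these changes too. In the same way, the sentence on distributions at both times may only mean that they are inspected to choose between the t and rank-sum tests, not that enrollment values are tested.

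It is further tempting to say that the trial lacks power for its obesity aim, or would miss even complete prevention of the average post-cessation gain quoted in the Background (2.8 kg in men, 3.8 kg in women). The first statement needs SDs the article does not give, and it concerns endpoints on which the trial was not sized. The second holds under the assumptions for 2.8 kg (28-48% power on raw means) but not clearly for 3.8 kg: 3.8/1.467 − 1.96 = 0.63 gives about 74% at SD 10, and 3.8/2.053 − 1.96 = −0.11 gives about 46% at SD 14. Those gains also refer to people who quit unaided, whereas participants here had clinic treatment and had already gained weight before enrollment.

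Finally, an unadjusted comparison of randomised groups is valid, and covariate detail is often left to a full protocol or analysis plan, which is not shown. All of this stands and limits the point. It does not remove the mismatch between the listed endpoint and the named variable, or the unclear contrast.

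**Conclusion.** The point holds as a question of endpoint wording and efficiency. The article lists BMI and names weight, and its analysis sentence can be read as a comparison of levels or of changes. If the literal reading were applied, a 2 kg difference in weight would be detected with roughly 16-28% power, against 59-100% on change and 61-100% with baseline adjustment. These figures are conditional on that reading, on a weight SD of 10-14 kg, on a correlation of 0.90-0.97 and on about 93 per arm. The direction needs only a correlation above 0.5; the size depends on the assumed values. The endpoints are secondary, so the primary conclusion on adiponectin is unaffected. But they are the measures that bear directly on the first-named aim, and the improvement costs nothing in data, so the wording should be changed.

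**What to change.** Reword Items analyzed and analytical methods so that it matches the Secondary endpoints section:

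- BMI and abdominal circumference at 9 months are each compared between assigned groups by a linear model, with the enrollment value of the same measure and the minimisation factors (age, sex, FTND score, prior weight gain, fear of weight gain) as covariates.
- The result is reported as a mean difference with a two-sided 95% confidence interval.
- Weight by group is given as description.
- Enrollment values are described by group and not tested.

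The cost is a change of wording. Weight, BMI and abdominal circumference are already measured at enrollment and at 9 months, and the covariates are already recorded for the allocation. No extra visit, sample or participant is needed. Recruitment was still under way when the article was submitted; the change should be fixed and dated before group outcomes are examined.

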## Methods/design

### Design and sample size

This trial will be a multicenter, prospective, parallel-group randomized controlled trial. Participants will be assigned either to a group receiving nutritional guidance (once every 3 months) or to a group not receiving nutritional guidance. We chose 3-monthly visits because nutritional guidance typically continues for about 6 months. In addition, a previous study reported that frequent visits have a greater effect on weight gain and that follow-up is needed at least once every 3 months [15]. Participants will be enrolled for 3 years after the trial is approved by the Central Ethics Review Committee. The total duration of the trial will be 6 years (scheduled duration: April 2016 to March 2022).

Our target enrollment is 250 participants (125 individuals in the control group, 125 individuals in the intervention group). No similar clinical studies exist to serve as a reference. Although the exact sample size cannot be calculated, it has been estimated as follows:

In previous studies by our group, changes in adiponectin levels had served as the primary endpoint, and the standard deviation (SD) for changes in adiponectin levels (defined as the percentage of change in adiponectin levels before and after treatment, with the adiponectin level prior to treatment representing 100%) was 20%. We envision a similar approach for the current trial, and the SD is set at 20% to compare the percentage of change in adiponectin levels in the two groups (individuals who do not receive nutritional guidance vs. individuals who do). In order to detect a 10% difference between the assigned groups (effect size: 0.5) at a two-tailed alpha level of 5%, with a power of 80% and an adjustment for multiple primary endpoints, each group will need to consist of 82 individuals. Assuming a 25% drop-out rate during follow-up, based on data amassed from the SC clinic, 110 participants would need to be enrolled in each group. In light of the aforementioned estimates and other factors for error, the required enrollment would ultimately be a total of 250 individuals who visit the SC clinic, or approximately 125 individuals in each group.

The study’s inclusion and exclusion criteria are outlined in Table 1. The participants must meet all of the inclusion criteria and none of the exclusion criteria.

**Table 1 Tab1:** Inclusion and exclusion criteria

Inclusion criteria	

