### Randomization

Prior to beginning this trial, the University Hospital Medical Information Network’s Internet Data and Information Center for Medical Research will be asked to create a central assignment system using the Electronic Data Capture (EDC) system. Once written consent is obtained from an individual who meets the inclusion criteria, and a lead investigator has verified that the individual meets all of the eligibility criteria and none of the exclusion criteria, the participant’s information will be registered in the EDC system. After registration, the EDC system will assign patient numbers that do not include the participant’s personal information. Immediately after entry, the EDC system will randomly assign the participants to one of two groups (the group receiving nutritional guidance or the group not receiving nutritional guidance) via dynamic allocation. A lead investigator (or study chair) and the study office of the Kyoto Medical Center will be notified of the patient numbers and the group assignments. Based on the EDC system assignment, a lead investigator will schedule nutritional guidance for individuals receiving nutritional guidance and a visit 9 months later for individuals not receiving nutritional guidance. Registration in the EDC system allows adjustments for confounding factors (age, sex, the FTND score, weight gain (kg) before and after SC, and the fear of gaining weight according to a survey) between groups. The participants will be randomized by minimization (a method of dynamic allocation).

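### The stated two-sample test leaves out the five minimization factors and uses baseline adiponectin only through the change, so it gives away precision wherever these predict the outcome

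*Protocol article*

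**What the plan says.** - **Allocation.** The Randomization section uses dynamic allocation by minimization. The factors to be balanced are "age, sex, the FTND score, weight gain (kg) before and after SC, and the fear of gaining weight according to a survey".
- **Baseline.** Adiponectin is in the list of items measured both at enrollment and 9 months later.
- **Analysis.** Under Items analyzed and analytical methods, changes from enrollment to 9 months are compared between groups, and "a *t* test or a Wilcoxon rank-sum test will be performed". The adjustment for confounders mentioned under Randomization describes balancing at allocation. No covariate-adjusted analysis is stated anywhere in the article.
- **Sample size.** Under Design and sample size, "the SD is set at 20% to compare the percentage of change in adiponectin levels in the two groups". The calculation is "at a two-tailed alpha level of 5%, with a power of 80% and an adjustment for multiple primary endpoints", and concludes that "each group will need to consist of 82 individuals".
- **Interim.** After 125 participants have completed follow-up, the trial stops for efficacy if Z_prop exceeds 2.538 and for futility if it is below 0.698. How Z_prop is computed is not stated.

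**The concern.** Minimization makes the groups more alike on the chosen factors than simple randomization would. If those factors predict the outcome, the true sampling variance of the group difference falls. A two-sample t or Wilcoxon test does not know this and charges the full outcome variance, so its confidence interval is too wide and its level is below nominal.

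Baseline adiponectin is a separate matter. It is not a minimization factor, so leaving it out of the model does not distort the level. It costs precision only, because a change score uses the baseline less efficiently than regression on it does.

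The article gives reasons to expect some prognostic value. It calls the factors confounders, reports that a high FTND score goes with weight gain, links fear of weight gain to relapse, and describes adiponectin as responsive to both obesity and smoking. At stake are the precision of the primary result and, if Z_prop is built from this test, the chance of an early efficacy stop.

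**Working it through.** **Inputs from the article.** Difference 10 points, SD 20 points (percentage change), two-sided 5%, power 80%, 82 evaluable per group, 25% drop-out, 125 completers at the interim.

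**Assumed, because the article gives neither.** R², the share of variance in the adiponectin outcome explained by the minimized factors (0 to 0.30); and r, the correlation between baseline and 9-month adiponectin (0.6 to 0.95).

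**1. The plan's own figure.** n = 2(1.96 + 0.842)² × (20/10)² = 63 per group with no multiplicity adjustment. A Bonferroni split over two endpoints gives 77 and over three gives 84; 82 corresponds to a two-sided level of about 0.018. The article does not state the split. Drop-out: 82/0.75 = 109.3, so 110, as stated. The calculation takes no credit for covariates.

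**2. Minimized factors, formula for exact balance.** The unadjusted standard error is 20√(2/82) = 3.12. It is too large by the factor 1/√(1 − R²), and the true level is 2[1 − Φ(1.96/√(1 − R²))].
- R² = 0.10: 5.4% too large, level 3.9%.
- R² = 0.20: 11.8% too large, level 2.8%.

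**3. Minimized factors, simulated.** Real minimization does not balance exactly. The simulation used 4,000 trials per setting, 82 per arm on average, biased-coin probability 0.8, and four two-level factors plus one four-level factor with equal influence.

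| R² | SE used by t test | True SE | Type I error, t | Power, t | Power, adjusted |
|---|---|---|---|---|---|
| 0 | 3.12 | 3.07–3.08 | 4.5% | 89.2% | 89.2% |
| 0.10 | 3.12 | 2.96–2.98 | 4.3% | 89.9% | 91.7% |
| 0.20 | 3.12 | 2.77–2.81 | 3.0% | 91.8% | 95.0% |
| 0.30 | 3.12 | 2.65–2.67 | 2.4% | 92.1% | 96.4% |

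Simulation error is about √(0.05 × 0.95/4000) = 0.3 points on the level and √(0.9 × 0.1/4000) = 0.5 points on power. The level at R² = 0.10 is therefore not clearly separated from that at R² = 0; the fall at 0.20 and 0.30 is clear. The Wilcoxon test behaves alike (3.1% level and 90.1% power at R² = 0.20). The adjusted model's type I error was 4.5–5.5%.

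**4. Baseline adiponectin.** With equal variances at both times, the variance is σ²(1 − r²) for the baseline-adjusted model and 2σ²(1 − r) for the change score. The ratio is (1 + r)/2.

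| r | Ratio | Variance saved | Equivalent out of 164 |
|---|---|---|---|
| 0.6 | 0.80 | 20% | 33 |
| 0.8 | 0.90 | 10% | 16 |
| 0.9 | 0.95 | 5% | 8 |
| 0.95 | 0.975 | 2.5% | 4 |

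**5. Interim, if Z_prop is an ordinary Z from this test.** At effect size 0.5 with 62.5 per arm, the expected unadjusted Z is 0.5 × √(62.5/2) = 2.795, with SD √(1 − R²) under exact balance. Adjusted for the five factors, the mean is 2.795/√(1 − R²) and the SD is 1.
- Efficacy, P(Z > 2.538), R² = 0.10: Φ(0.257/0.949) = 61% unadjusted; Φ(2.946 − 2.538) = 66% adjusted.
- Efficacy, R² = 0.20: Φ(0.257/0.894) = 61% unadjusted; Φ(3.125 − 2.538) = 72% adjusted.
- Futility, P(Z < 0.698): 1.35% unadjusted and 1.23% adjusted at R² = 0.10; 0.95% and 0.76% at R² = 0.20.

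**The case against.** **The size is assumed.** This stands. The R² that matters is for percentage change, and taking the change may already remove much of what age and sex explain. At R² = 0 there is no loss.

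**The baseline gain may be small.** This also stands. Percentage change already uses the baseline. Treating the planned SD of change as 0.20 on the log scale with equal variances, r = 0.6–0.8 implies a between-person log SD of 0.20/√(2(1 − r)) = 0.22–0.32. If that SD were 0.4–0.6 (an assumption), r would be 0.88–0.94 and the saving about 6–3%, or 10–5 of 164 participants. A reader might infer from step 4 that some 33 participants are wasted; that is only the top of an assumed range.

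**The test is valid and matches the sample size.** True. A reader might infer that the trial is underpowered or prone to false positives. Neither follows: the test errs on the safe side, and unadjusted power at 82 per group and two-sided 5% is about 89%, above the planned 80%. The margin disappears if the unstated multiplicity split is three-way: 79% unadjusted, against 84–88% adjusted at R² = 0.10–0.20.

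**Wrongful futility stopping.** It is tempting to say that an effective intervention would more often be stopped as futile. At the planned effect the difference is 0.1–0.2 percentage points. Z_prop is also undefined, so any link from this test to the stopping rules is inferred.

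**Covariates belong in an analysis plan.** An unseen plan may name an adjusted model. But the article does not leave the method open: it names the two-sample test beside boundaries given to three decimals. The comment is on a stated choice.

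**Conclusion.** The point holds as a matter of efficiency. The article pairs minimization on five factors with an unadjusted test. That test is conservative to the extent that the factors are prognostic, and it makes less use of a measured baseline than it could. The direction is certain; the size is not.

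- At an assumed R² of 0.10–0.20, the standard error is about 5–12% too large, the type I error about 4.3–3.0%, and the power loss at 82 per group about 2–3 points.
- Baseline adjustment would save a further 2.5–20% of variance over r = 0.95 to 0.6, also assumed.
- If Z_prop comes from this test, the more noticeable interim consequence is the lower chance of crossing the efficacy boundary at the planned effect, about 61% against 66–72%.

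The simulated figures also assume a particular minimization scheme; the article does not give its cut-points or allocation probability. This is worth correcting, but it does not threaten the validity of the trial.

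**What to change.** Prespecify the primary analysis as a linear model of the adiponectin outcome on group, baseline adiponectin and the five minimization factors. Two scales would serve:
- keep percentage change, on which the 10-point difference and 20-point SD were set; or
- use log 9-month adiponectin with log baseline as covariate, and report the group ratio, so that a ratio of about 1.10 corresponds to the planned difference when the control group stays near its baseline.

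Derive the interim and final Z from this model and state that Z_prop is that statistic. Use the same approach for the continuous secondary endpoints, each with its own baseline, and keep the unadjusted t or Wilcoxon test as a sensitivity analysis.

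**Cost.** A change to the analysis text, fixed before any comparison by group. All the variables are already collected at enrollment, so no visits, assays or participants are added. Two things need care: moving to the log scale changes the effect measure and must be linked explicitly to the sample-size assumptions, and the sponsor should confirm that the enrollment blood sample is drawn before the group is known, since the article does not give the order.
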